The main research questions to be addressed include: (1) Will participants’ combat-related TR-PTSD and moral injury symptoms, and associated behavior and physiology, change after an intervention of 3DMR therapy compared with treatment as usual? (2) Will peripheral multiomic biomarkers related to traumatic stress (ie, blood and salivary proteomic and genomic profiles of neuroendocrine, immune-inflammatory responses, and microRNA) be modified by the 3MDR intervention and show utility for predicting patient outcomes posttreatment? (3) What are the 3MDR clinicians’, operators’, and participants’ perceived technology acceptance and usability of 3MDR on the CAREN system? (4) What is the overall participant experience of the 3MDR intervention and comparability to PTSD therapies that the participants had previously engaged in? (5) Will 3MDR clinicians and operators experience perceived or secondary traumatic stress, or a change in their professional quality of life as a result of delivering 3MDR?

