### Data Analysis

#### Objective 1: Effectiveness of 3MDR

The quantitative analysis strategy for this study will include a variety of descriptive, parametric, nonparametric, univariate, and multivariate approaches, as well as machine-learning techniques.

Descriptive statistics will be used to summarize demographic data of participants, including mean values, frequencies, and proportions.

Baseline between-group differences in sociodemographic, clinical, and neuropsychological variables will be assessed. For psychological outcomes, including self-reported PTSD symptom severity, anxiety and depression symptoms, and avoidance behavior, analyses will be conducted using mixed linear models. All of the analyses above will be carried out on an intent-to-treat basis. A two-tailed *P*<.05 will be considered statistically significant.

For preliminary assessment of the relation between treatment outcomes and relevant predicting

variables, exploratory regression analyses will be performed and a predicting variable will be considered to have potential predicting value in cases of *P*<.20. Predictors will then be combined in a regression model to determine which variables most strongly predict 3MDR treatment success. Missing data points, potentially due to missed visits or outcome measure abnormalities, will be handled with the last observation carried forward analysis of covariance [59].

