A partial least squares (PLS) regression [60] will be used to identify combinations of blood biomarker concentrations that may distinguish the three treatment groups. PLS is a multivariate data reduction technique that creates orthogonal latent variables describing the maximal covariance between a set of predictors (biomarkers) and response (patient outcome) variables [61]. Between-group comparisons will be evaluated post hoc by generating bootstrapped mean differences of the group saliences for all group pairs, followed by the derivation of bootstrap ratios and empirical *P* values. In addition, model prediction performance will be quantitated by evaluating the prediction accuracy and posterior probability from separate PLS-discriminant analyses (PLSDA) on each group pair. PLSDA will also be used to evaluate the differences in biomarker profiles between groups. For both tasks, PLS and PLSDA, the weighted contribution of individual biomarker loadings will be quantitated by bootstrapped resampling (5000 iterations), followed by the generation of bootstrapped ratios and empirical *P* values. For evaluation of correlations between blood biomarkers and patient outcomes, an out-of-sample, leave-two-out cross-correlation (R2) value will be calculated on the PLS model. Random forest–based feature selection will be used to select the most relevant biomarkers that could be used to differentiate treatment groups. The random forest machine-learning algorithm is robust, with low bias and a reduced chance for overfitting.

For qualitative data analysis, audio recordings will be professionally transcribed and thematically analyzed in NVivo 12 software [62]. Thematic analysis involves examining text in detail to identify recurring patterns (“themes”) through both inductive and deductive reasoning [63]. Open codes will be combined into preliminary patterns that focus on similarities and differences within and between audio recordings to reduce the number of codes and provide more focus for the secondary level of coding [63]. Within the secondary level of coding, more abstract concepts will be assigned to broader categories of themes, and the relations between these concepts will be explored and verified through key quotes. Results will be distributed to a sample of the participants for member checking to assure the accuracy and trustworthiness of the research team’s interpretation of themes.

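### If group membership is the PLS response, the bootstrap P values for between-group biomarker differences are not referred to a no-difference null and reject too often; the response and the groups also need defining

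*Protocol article*

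**What the plan says.** Research question 2 (Overall Aims) asks whether peripheral biomarkers will "be modified by the 3MDR intervention and show utility for predicting patient outcomes posttreatment". The PLS paragraph under Data Analysis, Objective 1, describes the analysis.

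- **Aim of the fit:** to "identify combinations of blood biomarker concentrations that may distinguish the three treatment groups".
- **Response block, as described in the next sentence:** PLS is said to find the "maximal covariance between a set of predictors (biomarkers) and response (patient outcome) variables".
- **Group comparison:** "Between-group comparisons will be evaluated post hoc by generating bootstrapped mean differences of the group saliences for all group pairs".
- **Source of the P values:** these bootstrapped differences. The same sentence has them "followed by the derivation of bootstrap ratios and empirical *P* values".
- **Out-of-sample check:** for the biomarker-outcome correlation, "an out-of-sample, leave-two-out cross-correlation (R2) value will be calculated on the PLS model". It is not attached to the group-salience comparison.

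The paragraph also plans PLS-discriminant analysis (PLSDA) on each group pair and a random-forest selection of biomarkers. A significance level appears one paragraph block earlier, after the psychological outcomes: "A two-tailed *P*<.05 will be considered statistically significant". Study Design and Setting, and Randomization and Blinding, define two randomised groups of 20. No third group is defined.

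**The concern.** A test of whether biomarker profiles differ between groups needs a reference distribution for what happens when they do not. PLS with group as the response picks the biomarker combination that covaries most with group. Some separation is found in any sample, including one with no true difference.

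Resampling participants with their labels kept reproduces that separation. The bootstrap distribution shows how stable the fitted axis is. It does not show how large a separation chance alone would give. A P value read from it is a test on data already used to choose the contrast.

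At stake is the answer to the first half of research question 2. A biomarker effect of 3MDR could be reported where there is none, and the Discussion presents these biomarkers as a novel part of the study.

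**Working it through.** **Inputs.** 20 per group (Study Design and Setting). Nominal two-sided 5% (taken over from the preceding text as the working level). The number of biomarkers *p* and their correlation are not in the text at hand, because the biomarker details are in an appendix; assumed *p* = 3 to 100 and correlation 0 to 0.6.

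**The plan's own figure.** The article states no error rate for this comparison, so there is none to reproduce. The group size does follow from its stated basis: 17/(1 - 0.10) = 18.9, rounded up to 19, and set at 20 with further allowance for attrition.

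**Step 1: two groups, what the statistic is.** Let *d* be the difference between the two biomarker mean vectors. The cross-product of the two centred group columns with the biomarkers has rows proportional to *d* and -*d*. Its group saliences are therefore (1, -1)/√2 = (0.707, -0.707) for any *d*, and their difference is always 1.414. It carries no biomarker information. After sign alignment, a bootstrap draw can only give +1.414 or -1.414. If a share *q* of draws flips sign:

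- empirical two-sided P = 2*q*, which is below .05 when *q* < 0.025;
- bootstrap ratio = 1.414/(2 × 1.414 × √(*q*(1-*q*))) = 1/(2√(*q*(1-*q*))), which exceeds 1.96 when *q* < 0.070.

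**Step 2: two groups, how often this happens under no difference.** For standardised, independent biomarkers each element of *d* has variance 2/20 = 0.1. A draw flips when the bootstrapped *d* points away from the observed one, so *q* ≈ Φ(-|*d*|/√0.1). The rule *q* < 0.025 becomes |*d*|²/0.1 > 1.96² = 3.84. With no group difference, |*d*|²/0.1 is chi-square on *p* degrees of freedom, so the false-positive rate is about P(χ²ₚ > 3.84):

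- *p* = 1: 5%
- *p* = 3: 28%
- *p* = 5: 57%
- *p* = 10: 95%
- *p* = 20: above 99.9%

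The rate is nominal with one biomarker and rises with the number over which the axis is chosen.

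**Step 3: two groups, simulation** (no difference, 600 trials, 600 bootstrap draws, empirical P < .05):

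| Biomarkers | corr 0 | corr 0.3 | corr 0.6 |
|---|---|---|---|
| 3 | 34% | 30% | 18% |
| 5 | 61% | 53% | 28% |
| 10 | 96% | 87% | 39% |
| 20 | 100% | 97% | 51% |
| 50 | 100% | 99.8% | 57% |

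The first column agrees with Step 2, a little higher at small *p* because the bootstrap variance at 20 per group is slightly too small.

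**Step 4: three groups, as the paragraph is worded** (20 per group). The result depends on how the draws are aligned, which the article does not say.

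- Sign alignment, or latent variable refitted in each draw: about 6-14% per pair and 15-48% for any pair, by empirical P.
- Latent variable fixed, or Procrustes alignment (10 to 100 biomarkers, correlation 0 to 0.3): 50-81% per pair and 91-100% for any pair, by empirical P.
- Bootstrap ratio above 1.96: 15-79% per pair.

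**Step 5: patient outcome as the response.** The same bootstrap gave 1-4% per pair, so no inflation. The axis is then not chosen to separate the groups.

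**Step 6: a null reference with group as the response.** Shuffling labels and refitting each time gave 3.5-8.0% (200 trials per setting; Monte Carlo standard error √(0.05 × 0.95/200) = 1.5 points). A pooled-null bootstrap with refit gave 4.3-5.5% per pair.

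**The case against.** The strongest reply is that the article does not fix enough to establish a fault. It calls the response patient outcome, and on that reading the test is not inflated. It leaves the term empirical P value undefined, and a full protocol or analysis plan could define it through permutation. It speaks of three groups, so two-group error rates are not those of the test as worded, and the two-group salience result counts sign flips under an alignment rule the article does not state. The comparison is labelled post hoc and stands beside PLSDA accuracy and random-forest selection. The significance sentence belongs to the psychological outcomes.

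Much of this stands. It limits the size that can be claimed and makes the point conditional on the response. It does not remove it. The stated aim is to distinguish treatment groups, and group saliences belong to a group-coded response block. For that reading the article does more than stay silent: it names bootstrapped salience differences as the source of the P values. Every group-response implementation examined was above 5%. If patient outcome was meant, the paragraph contradicts its own aim and must be reconciled.

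Three stronger readings are tempting and are not supported:

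- **That identical groups would come out different almost regardless of the data.** That needs two groups and about 10 or more weakly correlated biomarkers, none of which the paragraph states.
- **That the individual biomarker loadings share the fault.** Simulated rates by empirical P were about 1-14%, which is too weak and too dependent on implementation to claim.
- **That the trial's main conclusion is at risk.** The sample size rests on clinician-rated PTSD symptoms, and no listed hypothesis names biomarkers.

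**Conclusion.** The point holds conditionally. With group membership as the PLS response, the stated bootstrap is centred on an already maximised separation and its P values are too small.

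Against a nominal 5%, the false-positive rate is about 18-100% with two groups. With three it is about 6-14% per pair and 15-48% for any pair by empirical P under sign alignment or refit, and 50-81% per pair with a fixed or Procrustes-aligned latent variable. Bootstrap ratios generally give more false positives in the three-group case. With the two randomised arms the salience difference is a constant and cannot answer the question at all.

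These figures assume 20 per group, Gaussian biomarkers, and the biomarker numbers and correlations stated above, which the article does not give. With patient outcome as the response there is no inflation. The matter is worth correcting, but it concerns a secondary biomarker analysis and leaves the primary PTSD comparison untouched.

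**What to change.** 1. Reconcile the text first. State whether the PLS response is group membership or patient outcome, and define the three treatment groups against the two randomised arms. If a third group arises from the crossover, groups share participants and a simple shuffle of arm labels does not apply to it.
2. Take the between-group P value from a permutation test at the pre-crossover comparison of the randomised arms. Shuffle the arm label across whole participants, not individual samples. Refit the full PLS or PLSDA each time. Compare the observed singular value, or the cross-validated PLSDA accuracy, with that distribution.
3. Keep the bootstrap for stability and intervals only, and do not convert bootstrap ratios of group saliences into P values.

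The cost is a few sentences of analysis wording and some computing time. No new data are needed. Fewer biomarker findings will reach significance.

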**Methods:**

This is a mixed-methods waitlist controlled crossover design randomized controlled trial. Participants include both CAF-SMs and veterans (N=40) aged 18-60 years with combat-related TR-PTSD (unsuccessful experience of at least 2 evidence-based trauma treatments). Participants will also include clinicians and operators (N=12) who have been trained in 3MDR and subsequently utilized this intervention with patients. CAF-SMs and veterans will receive 6 weekly 90-minute 3MDR sessions. Quantitative and qualitative data will be collected at baseline and at 1, 3, and 6 months postintervention. Quantitative data collection will include multiomic biomarkers (ie, blood and salivary proteomic and genomic profiles of neuroendocrine, immune-inflammatory mediators, and microRNA), eye tracking, electroencephalography, and physiological data. Data from outcome measures will capture self-reported symptoms of PTSD, moral injury, resilience, and technology acceptance and usability. Qualitative data will be collected from audiovisual recordings of 3MDR sessions and semistructured interviews. Data analysis will include univariate and multivariate approaches, and thematic analysis of treatment sessions and interviews. Machine learning analysis will be included to develop models for the prediction of diagnosis, symptom severity, and treatment outcomes.

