### Sample Size

A sample size calculation was conducted using G*Power 3 [55], based on the primary hypothesis that 3MDR would result in significantly lower clinician-rated PTSD symptoms as compared to treatment as usual. To detect a significant interaction with at least a medium effect size, a minimal sample size of 17 participants was determined for each group. Because of an estimated 10% dropout and some attrition at measurements, the sample size was set at 20 participants in each group (Cohen f=1.0) using general linear modeling with one within-subjects factor (2 time points) and one between-subjects factor (2 interventions), and assuming a correlation of r=0.5 between the repeated measures, an α-level of .05, and a power (1 – β) of 0.8.

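### The random forest's reduced chance of overfitting does not support its use for choosing biomarkers on about 40 people

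*Protocol article*

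**What the plan says.** Research question 2 (Overall Aims) asks whether peripheral biomarkers will "be modified by the 3MDR intervention and show utility for predicting patient outcomes posttreatment". The biomarker analysis is described in Data Analysis, Objective 1, and has two parts.

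- **Partial least squares (PLS) and PLS-discriminant analysis.** Group comparisons and individual biomarker loadings get bootstrap ratios and empirical P values, with 5000 resamples for the loadings. The relation between blood biomarkers and patient outcomes gets an out-of-sample, leave-two-out R2.
- **Random forest.** It is to "select the most relevant biomarkers that could be used to differentiate treatment groups". The one sentence in support is: "The random forest machine-learning algorithm is robust, with low bias and a reduced chance for overfitting".

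The number of people is small: "Participants include both CAF-SMs and veterans (N=40) aged 18-60 years", in two randomised groups of 20. The number of candidate biomarkers is not in the text shown, which refers to an appendix for the details.

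**The concern.** Averaging many trees limits how far the forest's predictions follow noise. Choosing markers is a different operation. The markers with the highest importance are, in part, those whose chance differences between the arms happened to be largest in these 40 people. Averaging trees built on the same people does not remove that chance.

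There are two consequences. A ranking always has a top, so a rule based on rank returns names whether or not any marker differs. And once everyone has helped choose the markers, out-of-bag accuracy from a forest refitted on them is no longer an independent check, because each person left out of a tree had already influenced which markers it could use.

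At stake is part of the answer to research question 2. The Conclusions of the abstract say the results will inform a full-scale trial, so a list of differentiating markers that a reader believes to be protected against overfitting could be carried further than it deserves.

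**Working it through.** **The plan's own figure.** The disputed sentence contains no number. The sample size it works on can be checked. Sample Size states that "a minimal sample size of 17 participants was determined for each group" for a medium effect, with 2 groups, 2 time points, r = 0.5, alpha 0.05 and power 0.8. Reading medium as f = 0.25 (by convention), the noncentrality is

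λ = f² × N × m / (1 − r) = 0.0625 × 34 × 2 / 0.5 = 8.5, with 1 and 32 degrees of freedom,

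which gives power 0.807 at N = 34, or 17 per group. Then 17 / 0.9 = 18.9, rounded up to 19 and set at 20. So 20 per group reproduces. (The f = 1.0 printed in that section would need only 6 people in all. It is not used here.)

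**Why chance markers reach the top.** With p independent markers and no arm difference, the chance that at least one differs at P < .05 is 1 − 0.95^p: 0.40 for 10 markers, 0.64 for 20, 0.92 for 50 and 0.99 for 100. Selection picks out exactly these markers.

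**Simulation with identical arms.** Inputs from the document: two arms of 20. Assumptions: panels of 10 to 500 independent standard normal markers; a 150-tree forest; markers ranked by impurity importance; the top 5 kept and the forest refitted on them. There were 40 simulated trials per panel size, and 20 at 500 markers. The true accuracy is 0.50.

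| Markers | Out-of-bag, all markers | Out-of-bag after top 5 | Trials with 0.70 or more after selection | Same 5 markers, new people | Selection repeated in each of 5 folds |
|---|---|---|---|---|---|
| 10 | 0.46 | 0.56 | 10% | 0.50 | 0.49 |
| 20 | 0.45 | 0.61 | 23% | 0.50 | 0.50 |
| 50 | 0.44 | 0.67 | 43% | 0.50 | 0.50 |
| 100 | 0.43 | 0.71 | 60% | 0.50 | 0.50 |
| 500 | 0.44 | 0.76 | 85% | 0.50 | 0.47 |

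The forest with all markers shows no optimism out of bag. The optimism appears only when selection and assessment use the same people, and it disappears when selection is repeated inside each fold.

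**Sensitivity.**
- A separately coded forest (100 trees, 60 trials per setting) gave 0.57, 0.62, 0.67 and 0.70 after selection for 10, 20, 50 and 100 markers, and 0.50 to 0.51 in new people.
- Keeping the top 10 from panels of 50, 200 and 1000 gave 68%, 77% and 81%, against 50–51% in new people.
- With markers correlated in blocks of five (correlation 0, 0.5, 0.8), accuracy after keeping the top 5 was 0.61, 0.62, 0.60 for 20 markers; 0.67, 0.67, 0.65 for 50; and 0.74, 0.72, 0.68 for 200. Correlation reduces the optimism modestly.
- A rule that keeps every marker of above-average importance would name about 4, 8, 19, 37 and 180 markers from panels of 10, 20, 50, 100 and 500 with no true difference.

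**With a null reference.** When a marker is named only if its importance exceeds the 95th percentile of the maximum importance under no difference, some marker is named in about 2% of null trials (20 markers) and 1% (50 markers), from 150 trials each. Ranking names 5 markers in 100% of them.

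**The case against.** The strongest reply is that the simulated procedure is not in the article. No top-5 rule, importance measure, refit or post-selection accuracy is stated. A permutation or shadow threshold is itself a form of random forest feature selection and would fit the existing sentence. Such details may stand in a fuller plan that is not shown, so their absence alone is no finding. This stands, and it limits the point to the support the article does state.

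Second, a reader might infer that the forest has no protection against overfitting at this sample size. The documents do not support that charge: the sentence claims only a reduced chance, which is comparative, and the forest with all markers scored 0.43 to 0.46 out of bag under no effect, so it was not optimistic.

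Third, the PLS and PLS-discriminant analyses in the same section have bootstrap P values that also address group differences. The forest list is therefore not the only answer to research question 2. That is right, but those P values do not apply to the markers the forest selects.

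Fourth, none of the four hypotheses concerns biomarker differences between arms, and the sample size rests on clinician-rated PTSD symptoms. This bears on importance. It does not make the stated support fit the selection step.

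**Conclusion.** The point holds in a limited form. The one property cited for the forest selection concerns prediction and does not protect the choice of markers on about 40 people. A fuller plan elsewhere would not change what that sentence can support.

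If markers are ranked and the top ones kept, markers can be named when the arms are identical. Accuracy assessed afterwards in the same people then averages about 0.56 at 10 markers and 0.76 at 500, against 0.50 in new people. These figures rest on an assumed panel size, an assumed top-5 rule, an assumed refit and independent markers. With a small panel the optimism is small.

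A reader might go further and conclude that the plan will name markers even when 3MDR changes none. That is certain only under a rule based on rank, and the article states no rule; under a null threshold it happened in about 1–2% of simulated trials. The step is secondary and exploratory, and the primary PTSD comparison does not depend on it. The change is worth making because it is cheap.

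**What to change.** - Limit the overfitting sentence to prediction, or delete it.
- Keep a marker only if its importance exceeds a reference from label-permuted data or shadow copies of the markers, permuting arm labels by participant.
- For any accuracy that is reported, repeat the selection inside each resample or fold, and give each marker's selection frequency.
- If this is not done, label the selected list hypothesis-generating.

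The cost is a few sentences in the analysis section and some computing time; data collection is unchanged. The downside is that the list may be short or empty, which is the honest result if no marker differs.
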